**9-3. Status of investigational drug administration and concomitant treatment**

1) Administration of investigational drug

The date and time of administration of the investigational drug should be noted in the case report form. If administration of the investigational drug is discontinued, the reason should be stated in the case report.

2) Status of concomitant treatment

For all concomitant medications and concomitant therapies administered to the subject from Week 1 to the time of completion or discontinuation of the investigational drug (4 weeks after the last administration), the daily dose, route of administration, start and end dates, and purpose of administration should be noted in the case report.

**9-4. Efficacy parameters**

**9-4-1. Antigen-specific antibody immunoreaction tests (NY-ESO-1 and XAGE-1b)**

Blood samples will be drawn at baseline, every 4 weeks after 5, 9, and 12 weeks if possible, and every 4 weeks from the 9th dosing date for maintenance dosing, and at the time of discontinuation of the study, and measured by an external laboratory. However, on the day of administration of the investigational drug, blood should be drawn prior to administration of the investigational drug. If administration of the investigational drug is discontinued, blood should be drawn at the time of discontinuation of administration, and every 4 weeks after discontinuation if possible. Measurement results will be submitted directly to the data center from an external laboratory.

**9-4-2. Regulatory T cell tests (FOUR-COLOR FOXP3 test, CD4/CD25/CCR4 test and MLA CD45 gating)**

Peripheral blood will be used to evaluate the decrease in the number of activated regulatory T cells by immunological monitoring. For this purpose, blood samples will be drawn at baseline, every 4 weeks after 5, 9, and 12 weeks when possible, and every 4 weeks after the 9th dose date during maintenance dosing, and at the time of discontinuation of the study, and measured by an external laboratory. However, on the day of administration of the investigational drug, blood should be drawn prior to administration of the investigational drug. If administration of the investigational drug is discontinued, blood should be drawn at the time of discontinuation of administration, and every 4 weeks after discontinuation if possible. Measurement results will be submitted directly to the data center from an external laboratory.

**9-4-3. CT and MRI**

Measurements will be taken at baseline and at Week 12. Thereafter, it will be performed every 12 weeks. It will also be performed every 12 weeks after discontinuation of the investigational drug if possible, and measurements will be taken at the time of discontinuation of the study.

The CT or MRI scan should be performed using the same model at each site and under the same imaging conditions for each subject as far as possible.

The cases judged as CR or PR by the RECIST method are objectively and uniformly judged by the Central Evaluation Committee of Imaging, which is a third-party organization.

The investigator submits the image data of cases judged as CR or PR to the Central Radiological Evaluation Committee at an appropriate time in accordance with the "Procedures for Central Radiological Evaluation," which is separately stipulated. If the judgment of the investigator and that of the Central Radiological Evaluation Committee differ, the judgment of the Central Radiological Evaluation Committee shall be the final evaluation.

**9-4-4. Survival surveys and post-treatment**

Survival period of patients who did not receive maintenance dosing and those who received maintenance dosing but discontinued it will be investigated until the end of the clinical trial as described in "14-3. In case of death, the date of death and the reason shall be noted in the case report form”.

If post-treatment was given, the details of the treatment, its duration, efficacy, and duration of response shall be investigated.

**9-4-5. Tumor markers (optional)**

Measure at baseline and week 12. Thereafter, it should be measured every 12 weeks. Also, after discontinuation of the investigational drug, it should be conducted every 12 weeks as much as possible. The measurement results should be documented in the case report form.

However, the implementation of tumor marker measurement and the items of tumor markers to be measured are optional.

**9-4-6. Evaluation of regulatory T cells (optional)**

Mononuclear cells in peripheral blood and tumor tissue will be isolated and immunological monitoring will be used to assess the decrease in the number of activated regulatory T cells. For this purpose, blood samples will be drawn at baseline, every 4 weeks after 5, 9, and 12 weeks if possible, and every 4 weeks after the 9th dose date during maintenance dosing, and at the time of discontinuation of the study, and measured by an external laboratory. However, on the day of administration of the investigational drug, blood should be drawn prior to administration of the investigational drug. If administration of the investigational drug is discontinued, blood should be drawn at the time of discontinuation and every 4 weeks after discontinuation if possible. One or two additional pieces of tumor tissue will be collected at the time of endoscopy or other tissue biopsy as part of routine medical care. Results are submitted directly to the data center.

**9-4-7. Antigen-specific antibody immunoreactivity testing (for antigens other than NY-ESO-1 and XAGE-1b) (optional)**

Blood samples will be drawn at baseline, every 4 weeks after 5, 9, and 12 weeks if possible, and every 4 weeks from the 9th dose date for maintenance dosing, and at the time of discontinuation of the study, and measured by an external laboratory. However, on the day of administration of the investigational drug, blood should be drawn prior to administration of the investigational drug. If administration of the investigational drug is discontinued, blood should be drawn at the time of discontinuation of administration, and every 4 weeks after discontinuation if possible. Blood samples for this test should be collected in conjunction with the antigen-specific antibody immunoreactivity tests (NY-ESO-1 and XAGE-1b) described in 9-4-1. The results are submitted directly to the data center from an external laboratory.

**9-4-8. Antigen-specific cellular immuno-correspondence testing (arbitrary)**

Blood samples will be drawn at baseline, 7, 12 weeks, every 4 weeks after 12 weeks, if possible, every 4 weeks after the 9th dose at the maintenance dose, and at the time of discontinuation of the study, and the results will be measured at an external laboratory. However, on the day of administration of the investigational drug, blood should be drawn prior to administration of the investigational drug. If administration of the investigational drug is discontinued, blood should be drawn at the time of discontinuation of administration, and every 4 weeks after discontinuation if possible. Measurement results will be submitted directly to the data center from an external laboratory.

**9-4-9. Cytokine productivity evaluation (optional)**

Blood samples will be drawn at baseline, 7, 12 weeks, every 4 weeks after 12 weeks, if possible, every 4 weeks after the 9th dose at the maintenance dose, and at the time of discontinuation of the study, and measured by an external laboratory. However, on the day of administration of the investigational drug, blood should be drawn prior to administration of the investigational drug. If administration of the investigational drug is discontinued, blood should be drawn at the time of discontinuation of administration, and every 4 weeks after discontinuation if possible. Measurement results will be submitted directly to the data center from an external laboratory.

**9-4-10. Analysis of immune response cells and control cells (optional)**

Blood samples will be drawn at baseline, 7, 12 weeks, every 4 weeks after 12 weeks, if possible, every 4 weeks after the 9th dose at the time of maintenance administration, and at the time of discontinuation of the study, and measurements will be performed at an external laboratory. However, on the day of administration of the investigational drug, blood should be drawn prior to administration of the investigational drug. If administration of the investigational drug is discontinued, blood should be drawn at the time of discontinuation of administration, and every 4 weeks after discontinuation if possible. Measurement results will be submitted directly to the data center from an external laboratory.

**9-4-11. Immunohistochemistry (optional)**

Tissue biopsy specimens from past surgical extractions or tissue biopsies obtained during endoscopy as part of routine medical examinations are used for staining. When possible, one or two additional biopsies should be obtained from the tumor site in addition to the biopsies normally required for diagnosis during endoscopy.

Both specimens collected are used for pathological diagnosis at each facility. After diagnosis, unstained specimens are prepared from the stored blocks. Stained results are submitted directly to the data center from an external laboratory.

**9-4-12. Gene analysis (optional)**

Blood samples are collected at baseline (before the start of study drug administration) and assayed by an external laboratory. The results will be submitted directly to the data center from the external laboratory. 9-5.

**9-5. Safety-related items**

**9-5-1. PS (Performance status)**

Observe at baseline, at each dose of study drug, and at Weeks 9 and 12. It will also be observed at the time of discontinuation of dosing and at the time of discontinuation of the study during the period of study drug administration. However, for the date of administration of the investigational drug, observation will be conducted prior to administration of the investigational drug. The score shall be in accordance with the definition of Performance Status Scale/Scores ECOG.

**9-5-2. Vital signs (blood pressure, pulse rate, temperature, respiratory rate)**

Observed at baseline and at each dose of study drug, before administration, 30 minutes, 1 hour, 1.5 hours, at the end of administration, 30 minutes and 1 hour after the end of administration. Observations will also be made at Weeks 9, 12, at the time of discontinuation of dosing, and at the time of discontinuation of the study during the period of study drug administration. The observation results will be documented in the case report form.

**9-5-3. Body weight**

Body weight shall be measured at baseline, at each dose of study drug, and at Weeks 9 and 12. It will also be measured at the time of discontinuation of administration and at the time of discontinuation of the study during the study drug administration period. However, on the day of administration of the investigational drug, measurement shall be performed before administration of the investigational drug. The measurement results shall be documented in the case report form.

**9-5-4. General blood tests**

Blood tests shall be performed at baseline, each time the investigational drug is administered, and at Weeks 9 and 12. Also, at the time of discontinuation of dosing and at the time of discontinuation of the study. In addition, the test shall be performed at Week 12 after the last dose of the investigational drug. However, for the date of administration of the investigational drug, the test shall be conducted prior to administration of the investigational drug. The test results shall be documented in the case report form. The test items shall be as follows

1) Hematological tests

Red blood cell count, hemoglobin, hematocrit, white blood cell count, white blood cell fraction, platelet count

2) Blood biochemical tests

AST (GOT), ALT (GPT), ALP, LDH, total protein, albumin, total bilirubin, urea nitrogen, creatinine, uric acid, sodium, potassium, chlor, calcium, phosphorus

**9-5-5. Thyroid function test**

Tests shall be performed at baseline, Week 12, at the time of discontinuation of treatment, and at the time of discontinuation of the study during the period of study drug administration. However, for the date of administration of the investigational drug, the test shall be performed prior to the administration of the investigational drug. The test results will be documented in the case report form. The test items shall be as follows

FT3, FT4, TSH

**9-5-6. Urinalysis**

Perform at baseline, 2 and 12 weeks. At maintenance dosing, testing will be performed every 12 weeks from the 9th dosing date. However, for the date of administration of the investigational drug, the test shall be performed prior to the administration of the investigational drug. In addition, the test shall be performed at the time of discontinuation of administration and at the time of discontinuation of the clinical trial during the period of administration of the investigational drug. The test results shall be documented in the case report form. The test items shall be as follows

1) Urine qualitative

Protein, sugar, urobilinogen, occult blood

**9-6. Pharmacokinetics (Phase Ia part)**

Before the first dose, at the end of administration, 24 hours, 72 hours, and 168 hours after the end of administration (7 days later, before the second dose), at the end of the fifth dose, 168 hours after the end of administration (7 days later, before the sixth dose), before the eighth dose, at the end of administration, 24 hours, 72 hours, and 168 hours (7 days later), 14 days later, and 28 days later Blood samples are taken at 24 hours, 72 hours, 168 hours (after 7 days), 14 days, and 28 days after the end of administration, and the results are measured at an external laboratory. The results are submitted directly to the data center from the external laboratory. 10.

**10. Safety handling**

**10-1. Definitions**

**10-1-1. Definition of clinical examination value abnormalities and abnormal changes**

For blood and urine tests, normality and abnormality are determined for each measured value of each item, and then compared to the baseline to determine the presence or absence of abnormal fluctuations. If the normal range is not set, the investigator shall set it.

The investigators will determine whether or not there are any abnormal fluctuations based on the laboratory values before the first administration and the laboratory values performed after the administration. If an abnormal variation is detected, it should be treated as an adverse event in the laboratory values and entered in the case report form.

As with laboratory values, determine whether there are any abnormal changes in body weight, vital signs, etc. If abnormal changes are found, treat them as adverse events and enter them in the case report form.

**10-1-2 Definition of harmful events and side effects (harmful events with a negative causal relationship)**

An adverse event is any unfavorable medical event that occurs in a subject receiving an investigational drug. In other words, any unwanted or unintended signs (including abnormal changes in laboratory values), symptoms, or illnesses that occur when the investigational drug is administered, regardless of whether or not there is a causal relationship with the investigational drug. In addition, adverse drug reactions (adverse events for which a causal relationship cannot be denied) are all adverse events other than those judged to have a "no relationship" causal relationship to the investigational drug.

Signs, symptoms, and abnormal changes in laboratory values associated with a disease (diagnostic name) shall be treated as adverse events with the diagnostic name. However, if an atypical or extremely severe sign or symptom occurs in the disease, the individual sign or symptom as well as the diagnosis should be treated as an adverse event.

The observation period for adverse events will be from the date of the first dose of study drug to 12 weeks after the last dose. However, for Grade 3 or higher non-hematologic toxicity, the observation period for adverse events shall be up to 24 weeks.

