**1-3-1-2. Toxicity test**

Toxicity was evaluated using crab-eating macaques, in which antigen expression was observed in tissues similar to those of humans. As for acute toxicity, no deaths or changes in general condition were observed at doses up to 100 mg/kg, and the approximate lethal dose was considered to be 100 mg/kg or higher. No effects of the test substance were observed after repeated weekly dosing for up to 13 weeks, and the non-toxic dose was 40 mg/kg/week, the highest dose studied in this study. The AUC0-7d at the non-toxic dose was more than 33 times higher than the AUC0-7d value at 8 doses of 1 mg/kg in the clinical study. In a study on embryo-fetal development, administration of 40 mg/kg/week to pregnant crab-eating macaques showed no general toxicity or reproductive effects in the mother. Furthermore, no effects on embryo-fetal development were observed, although there was some transfer of mogamulizumab to the fetus. In addition, no findings of local irritation were observed in the evaluation of the site of administration within each toxicity study.

Single and repeated administration studies in crab-eating macaques showed the production of anti-Mogamulizumab antibodies. Even in individuals that did produce anti-Mogamulizumab antibodies, there were no significant findings in toxicity studies, and anti-Mogamulizumab antibodies were not considered to pose a safety issue.

The decrease in CCR4-positive T cells observed in the toxicity study was based on the pharmacologic effects of mogamulizumab. In the single-dose study with a 12-month observation period, a recovery trend was observed, but the levels remained low throughout the observation period; in the 4-week repeat-dose study, a recovery trend was observed after approximately a 3-month withdrawal period, but the levels remained low at the last examination. However, no signs of toxicity were observed in either study, and the persistent decrease in CCR4-positive T cells was considered not to be a concern for developing toxicity.

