**7-2. Group-to-group transition and procedures in phase Ia part**

The following procedure will be used to transition from the 0.1 mg/kg dose group to the 0.5 mg/kg dose group and then to the 1.0 mg/kg dose group. The Clinical Trial Coordinating Committee will decide on the transition of dosing groups. However, the efficacy and safety evaluation committee will also evaluate if necessary.

(1) If no DLT occurs in any of the 3 patients in the 0.1 mg/kg dose group, the patient will be shifted to the 0.5 mg/kg dose group.

If one of the three patients in the 0.1 mg/kg group develops DLT, three more patients will be enrolled in the 0.1 mg/kg group; if three or more patients in the 0.1 mg/kg group develop DLT, the MTD will be 0.1 mg/kg and the study will be terminated. If DLT occurs in 2 or less cases, the patient will be shifted to the 0.5 mg/kg group.

(2) If no DLT occurs in any of the 3 patients in the 0.5 mg/kg group, the patient will be moved to the 1.0 mg/kg group.

If 1 of 3 patients in the 0.5 mg/kg group develops DLT, enroll 3 more patients in the 0.5 mg/kg group. If more than 3 patients in the 0.5 mg/kg group develop DLT, the MTD will be 0.5 mg/kg and Phase Ia will be terminated. /Kg group if there are 2 or less cases of DLT.

(3) If none of the 3 patients in the 1.0 mg/kg group develop DLT, the MTD will be greater than 1.0 mg/kg and the Phase Ia portion will be terminated.

If 1 of 3 patients in the 1.0 mg/kg group develops DLT, enroll an additional 3 patients in the 1.0 mg/kg group; if 3 or more patients in the 1.0 mg/kg group develop DLT, the MTD will be 1.0 mg/kg and Phase Ia will be terminated. If DLT develops in 2 or fewer patients, the MTD will be 1.0 mg/kg. If fewer than 2 cases of DLT occur, the MTD will be greater than 1.0 mg/kg and Phase Ia will be terminated.

If the MTD is determined, investigational drug administration in the dose group corresponding to the MTD will be discontinued.

The safety evaluation for transfer to the next group (DLT observation period) can be determined based on information and test results up to 28 days after the start of the investigational drug administration, but the final safety evaluation period will be up to 24 weeks after the last dose in each case.

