**10-2-6. Outcome**

Describe the outcome confirmed by 4 weeks after the last observation period of the adverse event (16 weeks (28 weeks for Grade 3 or higher non-hematologic toxicity) after the last administration date of the study drug). Follow-up of adverse drug reactions (adverse events for which a causal relationship cannot be ruled out) will be conducted until they are confirmed to have recovered or become mild.

1) Recovery (when the patient returns to the same level as before the first administration of the investigational drug)

2) Slightly improved (the worst is over, but not back to the same level as before the first dose of the investigational drug)

3) Unrecoverable (the worst has continued)

4) Severe sequelae (the adverse event has resolved but other related symptoms remain)

5) Death (if the adverse event resulted in death)

6) Unknown (when the patient is unknown)

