**10-3. Adverse event reporting and response**

Adverse events that must be reported are those that occur during the observation period of adverse events defined in "10-1-2. Definition of adverse events and adverse reactions (adverse events for which a causal relationship cannot be ruled out)" and "Serious adverse events" defined in "10-1-3. When such an adverse event occurs”, it should be reported in accordance with "10-3-1. Serious Adverse Event Reporting Procedures”.

In addition, if an adverse event that is not a serious adverse event but meets the criteria for DLT (defined in 8-3-1. Primary Endpoints) occurs in the Phase Ia portion, regardless of whether or not there is a causal relationship, the investigator should take appropriate measures, prepare a "Report on Adverse Events Related to Dose Increases" and promptly submit it to the Trial The report shall be promptly submitted to the Clinical Trial Coordinating Committee.

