**14-3. Completion of tests**

The clinical trial shall be terminated at the later of 1 year after the start of the last case of administration or 24 weeks after the last dose of the investigational drug.

After the clinical trial is terminated, the investigator shall notify the head of the institution in writing that the clinical trial has been terminated and report a summary of the results of the clinical trial in writing.

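### Trial closure, concomitant-drug recording and the adverse-event and serious-event windows follow time rules that do not fit together

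*Protocol*

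**What the plan says.** The Protocol sets its safety time limits in several places.

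- **Adverse-event window.** 10-1-2 states: "The observation period for adverse events will be from the date of the first dose of study drug to 12 weeks after the last dose". Grade 3 or higher non-haematological toxicity is observed to 24 weeks. Footnote *10 to Table 1 repeats both limits.
- **Outcome window.** 10-2-6 asks for the outcome confirmed by "16 weeks (28 weeks for Grade 3 or higher non-hematologic toxicity) after the last administration date of the study drug". 10-2-7 uses the same limits for the outcome date and grade.
- **Trial end.** 14-3 closes the trial at "the later of 1 year after the start of the last case of administration or 24 weeks after the last dose".
- **Concomitant treatment.** 9-3 asks for all concomitant drugs and therapies "from Week 1 to the time of completion or discontinuation of the investigational drug (4 weeks after the last administration").
- **Phase Ia safety period.** After setting the 28-day DLT decision, 7-2 adds that "the final safety evaluation period will be up to 24 weeks after the last dose in each case". It makes no distinction by grade or type of event.
- **Reporting duty.** 10-3 opens: "Adverse events that must be reported are those that occur during the observation period of adverse events defined in" 10-1-2, and joins this to the definition of serious events in 10-1-3.

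**The concern.** The type, frequency and severity of adverse events are a primary endpoint in both phases (8-1-1, 8-1-2). The recommended Phase II dose rests partly on Phase Ib safety (8-3-2). These results depend on how long events are collected, attributed and followed, and three of the time limits do not match.

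1. The trial can close before the last required outcomes are due.
2. Each event needs a causality judgement that considers other causes (10-2-8), but the full record of other drugs stops well before event collection does. 10-5-2 itself warns that severe skin disorders have appeared weeks after treatment ended.
3. A Phase Ia site can read weeks 13 to 24 after the last dose as inside the safety period under 7-2, yet closed to haematological events and to Grade 1-2 non-haematological events under 10-1-2. If 10-3 follows 10-1-2, a serious haematological event in week 14 carries no reporting duty under that section, while a serious Grade 3 non-haematological event in the same week does. 10-1-2 gives no reason for the difference.

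**Working it through.** **Inputs**

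| Rule | Section | Weeks after last dose |
|---|---|---|
| Adverse events, general | 10-1-2, footnote *10 | 12 |
| Adverse events, Grade 3 or higher non-haematological | 10-1-2, footnote *10 | 24 |
| Outcomes, general / Grade 3 or higher non-haematological | 10-2-6, 10-2-7 | 16 / 28 |
| Concomitant treatment | 9-3 | 4 |
| Final safety period, Phase Ia | 7-2 | up to 24 |
| Trial end | 14-3 | 24, or 1 year after the last patient's start if later |
| Last scheduled general blood test | 9-5-4 | 12 |

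**Step 1. The Protocol's own figures.** 10-2-6 adds 4 weeks to the observation period: 12 + 4 = 16 and 24 + 4 = 28. Both are reproduced, so the outcome windows agree with 10-1-2.

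**Step 2. Trial end against outcomes.** Let L be the weeks from the last patient's start to the last dose given to anyone in the trial, and take 1 year as 52 weeks. The trial ends at max(52, L + 24). The patient who receives that last dose needs outcomes to L + 28.

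| L | Trial end | Outcome due | Shortfall |
|---|---|---|---|
| 7 (eighth weekly dose, no maintenance) | max(52, 31) = 52 | 35 | 0 |
| 24 | max(52, 48) = 52 | 52 | 0 |
| 26 | max(52, 50) = 52 | 54 | 2 |
| 28 | max(52, 52) = 52 | 56 | 4 |
| 40 | max(52, 64) = 64 | 68 | 4 |

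The shortfall is 0 up to L = 24, L − 24 between 24 and 28, and 4 weeks from 28 on. For a patient whose last dose came d weeks before the trial's last dose, with L at least 28, it is (L − d + 28) − (L + 24) = 4 − d, which reaches 0 at d = 4. Only maintenance patients dosed at or near the trial's last dose are affected. Maintenance has no fixed end before the discontinuation criteria are met (7-1, 7-8), so L above 24 is possible.

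**Step 3. Concomitant treatment against event collection.** 12 − 4 = 8 weeks for the general window. 24 − 4 = 20 weeks for Grade 3 or higher non-haematological toxicity.

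**Step 4. 7-2 against 10-1-2.** 24 − 12 = 12 weeks (13 to 24) lie inside the 7-2 period but outside the 10-1-2 window, for haematological events of any grade and for Grade 1-2 non-haematological events.

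**Step 5. Reading 10-3.** The sentence joins the 10-1-2 observation period and the 10-1-3 definition with a plain conjunction, so it could mean events meeting both conditions or two separate categories. The next paragraph turns to events that are not serious but meet the DLT criteria. That makes serious events within the window the natural reading of the first paragraph.

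**The case against.** Several objections have force.

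- **7-2 may be an outer bound.** It speaks of a period up to 24 weeks and contrasts it with the 28-day DLT decision. The longest window in 10-1-2 is also 24 weeks, and the tiered rule is stated consistently elsewhere. 7-2 covers Phase Ia only. This stands: the mismatch is an ambiguity to settle, not a flat contradiction.
- **10-3 is loosely worded, and 18-4 helps.** 18-4 requires prompt reporting to the review committee of serious unpredictable reactions, with no time limit. It would be wrong to say that nothing is reportable after the window. But 10-4 lists haematological toxicity among the expected effects, so a serious haematological reaction need not count as unpredictable.
- **Other drug records exist.** 9-4-4 collects post-treatment, and 10-2-5 records treatment given for each event. Neither asks for all drugs taken before a late event, so the gap is partial but real.
- **The closure gap is narrow.** It concerns one class of event in the last few maintenance patients. This stands, and it sets the size.

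A reader might also infer more than the documents support.

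- **Outcome windows that match no other rule.** They are exactly 10-1-2 plus 4 weeks.
- **Late events left unresolved in general.** 10-2-6 follows events whose causal link cannot be excluded until they have recovered or become mild, without a week limit. That duty too can run past the end set in 14-3, but this is a closure problem, not a general lack of follow-up.
- **Late toxicity shown in macaques.** 1-3-1-2 does report that "a recovery trend was observed, but the levels remained low throughout the observation period", but the same paragraph notes no toxicity and concludes that the persistent decrease was not a toxicity concern.

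**Conclusion.** Three time rules need to be brought into line.

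1. **Trial end:** up to 4 weeks of outcome confirmation for Grade 3 or higher non-haematological toxicity can be lost. This happens only when the trial's last dose falls more than 24 weeks after the last patient's start, and only for patients last dosed within 4 weeks of that dose. It assumes that the last dose in 14-3 means the last dose in any patient.
2. **Concomitant drugs:** 8 weeks of general event collection, and 20 weeks for Grade 3 or higher non-haematological toxicity, lack a full drug record. This rests only on the stated windows.
3. **Safety and reporting window:** 12 weeks are open to two readings in Phase Ia. In both phases, serious events in the classes cut off at week 12 fall outside 10-3 on its natural reading.

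The Protocol does not allow an estimate of how many events would be missed or misattributed. It also does not support a demand to collect every adverse event to 24 weeks. The last scheduled general blood test is at week 12 and post-treatment is unrestricted (7-10), so later counts would be unsystematic and mixed with the effects of other therapy. The changes are cheap and bear on a primary endpoint, so they should be made.

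**What to change.** - **14-3:** replace 24 weeks after the last dose with 28 weeks. The end becomes max(52, L + 28), which covers every outcome due under 10-2-6 and 10-2-7.
- **9-3:** record concomitant drugs and therapies to the end of the applicable adverse-event window: 12 weeks, or 24 weeks where Grade 3 or higher non-haematological toxicity is still being observed.
- **7-2, 10-1-2 and footnote *10:** state whether the 24 weeks in 7-2 is only the outer limit of the tiered windows or applies to all events in Phase Ia, and use the same words in all three places.
- **10-3:** state that a serious event judged possibly related is reportable up to trial end, even if it occurs after week 12. Define possibly related as any 10-2-8 category other than no association, which matches how 10-1-2 defines an adverse drug reaction.

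The cost is a protocol amendment, additional CRF entries for later concomitant drugs and late serious events, and closure later by 0 to 4 weeks (0 when L is 24 or less, 4 when L is 28 or more). No new laboratory visits are needed, and patients are already followed for survival to trial end under 9-4-4.
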